#### Subgroup analyses

Exploratory subgroup analyses will examine potential effect modification by baseline cognitive severity and age group through inclusion of interaction terms in the mixed-effects models. These analyses are explicitly hypothesis-generating and will be interpreted as such.

### Qualitative process evaluation

#### Design and conceptual framework

A mixed-methods process evaluation is embedded within the trial to examine how the intervention is delivered, how participants and providers engage with it, and how contextual factors shape implementation. The evaluation is guided by the RE-AIM framework,^35^ supplemented by constructs from the Consolidated Framework for Implementation Research (CFIR)^46^ to capture multilevel influences on implementation.

##### Participants and data collection

Purposive maximum-variation sampling will be used to recruit a diverse subsample of stakeholders, including service users from both trial arms, caregivers, facilitators, supervisors and hospital administrators. Data collection methods include semistructured individual interviews and focus group discussions conducted approximately 3 months post-intervention (online supplemental file 3). Interviews and groups are conducted in English or Nigerian Pidgin by trained qualitative researchers who are independent of intervention delivery. Youth Research Team members co-facilitate selected sessions to minimise power differentials and enhance rapport.

### Data analysis

All qualitative data are audio-recorded, transcribed verbatim and anonymised prior to analysis. Framework Analysis is employed, allowing for deductive coding aligned with RE-AIM and CFIR domains alongside inductive identification of emergent themes. NVivo software is used to support data management and analysis. Qualitative findings are triangulated with quantitative data to construct an integrated implementation narrative explaining variability in engagement and outcomes.

### Health economics evaluation

#### Perspective and scope

An exploratory within-trial economic evaluation is undertaken to estimate the costs of delivering task-shifted CCT and to generate preliminary cost-effectiveness data. The primary analytic perspective is that of the public healthcare provider, with a secondary societal perspective incorporating participant and caregiver costs.

#### Measurement and valuation

Intervention costs are estimated using a micro-costing approach, capturing training, staff time, supervision, materials, facilities and digital infrastructure. Service utilisation and indirect costs are assessed using the adapted CSRI. Unit costs are derived from hospital finance departments, National Health Insurance Authority tariffs and published Nigerian health economic data. Costs are reported in 2026 Nigerian Naira and converted to international dollars for comparability.

#### Economic analysis

Given the pilot design, analyses prioritise transparency and estimation over decision rules. Cost–consequence analysis presents disaggregated costs alongside the full range of outcomes. Exploratory cost-effectiveness analyses estimate incremental cost per quality-adjusted life-year gained using EQ-5D-5L data. Uncertainty is characterised using non-parametric bootstrapping to generate cost-effectiveness acceptability curves. Details regarding the micro-costing approach and resource use categories are documented in online supplemental file 4.

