**Figure 1 F1:**
[figure not shown]
CONSORT flow diagram for the CognIFied pilot randomised controlled trial. CCT, compensatory cognitive training; CONSORT, Consolidated Standards of Reporting Trials.

**Table 1 T1:** SPIRIT schedule of enrolment, interventions and assessments

Study period	Screening	Baseline (T0)	Randomisation	Intervention period	3 months (T1)	6 months (T2)	12 months (T3)
Enrolment							
Eligibility screening (MINI 7.0)	✓						
Cognitive screening (BACS)	✓						
Informed consent	✓	✓					
Demographics and clinical history		✓					
Random allocation			✓				
Interventions							
CCT (12-weekly group sessions)				✓			
Enhanced recreational therapy (12-weekly group sessions)				✓			
Primary outcomes							
Recruitment and retention metrics	✓				✓	✓	✓
Intervention adherence (attendance)				✓	✓		
Acceptability (CSQ-8)					✓		
Intervention fidelity (audio coding)				✓			
Secondary outcomes							
Global cognition (BACS composite)		✓			✓	✓	✓
Functional capacity (UPSA-N)		✓			✓	✓	✓
Symptom severity (BPRS-18)		✓			✓	✓	✓
Disability (WHODAS 2.0)		✓			✓	✓	✓
Quality of life (MANSA, WHOQOL-BREF)		✓			✓	✓	✓
Social cognition (SCSQ-N)		✓					✓
Economic outcomes							
Resource use (CSRI)		✓					✓
Health utility (EQ-5D-5L)		✓					✓
Qualitative evaluation							
Interviews/ focus groups					✓		

BACS, Brief Assessment of Cognition in Schizophrenia; BPRS-18, Brief Psychiatric Rating Scale-18; CCT, compensatory cognitive training; CSQ-8, Client Satisfaction Questionnaire-8; CSRI, Client Service Receipt Inventory; EQ-5D-5L, EuroQol Five Dimensions Five Levels; MANSA, Manchester Short Assessment of Quality of Life; MINI, Mini-International Neuropsychiatric Interview; SCSQ-N, Social Cognition Screening Questionnaire-Nigeria; SPIRIT, Standard Protocol Items: Recommendations for Interventional Trials; UPSA-N, UCSD Performance-Based Skills Assessment; WHODAS 2.0, WHO Disability Assessment Schedule 2.0; WHOQOL-BREF, WHO Quality of Life-BREF.

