### Outcome measures and assessment schedule

#### Assessment schedule

Outcome assessments are conducted at four time points by trained research assistants who remain blinded to treatment allocation throughout the study. Baseline assessments (T0) occur within 2 weeks prior to randomisation. Post-intervention assessments are conducted at 3 months following randomisation (T1; ±2 weeks), corresponding to completion of the 12-session intervention period. Further follow-up assessments are conducted at 6 months (T2; ±2 weeks) and at twelve months (T3; ±4 weeks), the latter constituting the primary endpoint for longitudinal outcomes. The schedule of enrolment, interventions and assessments throughout the study period is detailed in table 1.

This extended follow-up period is intended to capture not only immediate post-intervention effects but also the durability of cognitive and functional changes over time, an issue of particular relevance for early psychosis interventions.

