#### Economic outcomes

Resource use and costs are assessed using an adapted Client Service Receipt Inventory (CSRI),^44^ capturing utilisation of formal healthcare services, informal care, non-orthodox care (including traditional and faith-based services) and productivity losses. Health-related quality of life is measured using the EQ-5D-5L^45^ to support exploratory cost–utility analyses.

A comprehensive summary of outcome domains, the specific instruments employed and their respective assessment schedules is provided in table 2.

**Table 2 T2:** Outcome domains, instruments and assessment time points

Outcome domain	Measure	Outcome type	Assessment time points
Feasibility	Recruitment rate	Primary	Screening to randomisation
	Retention rate	Primary	3, 6 and 12 months
	Session attendance	Primary	During intervention
Acceptability	Client Satisfaction Questionnaire-8	Primary	3 months
Implementation fidelity	CCT fidelity checklist (audio-coded)	Primary	During intervention
Global cognition	Brief Assessment of Cognition in Schizophrenia composite	Secondary	Baseline, 3, 6, 12 months
Functional capacity	UCSD Performance-Based Skills Assessment–Nigeria	Secondary	Baseline, 3, 6, 12 months
Psychiatric symptoms	Brief Psychiatric Rating Scale-18	Secondary	Baseline, 3, 6, 12 months
Disability	WHO Disability Assessment Schedule 2.0 (12-item)	Secondary	Baseline, 3, 6, 12 months
Quality of life	Manchester Short Assessment of Quality of Life	Secondary	Baseline, 3, 6, 12 months
	WHO Quality of Life-BREF (global items)	Secondary	Baseline, 3, 6, 12 months
Social cognition	Social Cognition Screening Questionnaire–Nigeria	Exploratory	Baseline, 12 months
Health-related quality of life	EQ-5D-5L	Economic	Baseline, 12 months
Resource use and costs	Client Service Receipt Inventory	Economic	Baseline, 12 months

CCT, compensatory cognitive training.

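### QALYs are to be built from EQ-5D-5L taken only at baseline and 12 months, so any non-linear change in utility in between is missed, with bias of unknown direction

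*Protocol article*

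**What the plan says.** Under Economic analysis, the protocol article states: "Exploratory cost-effectiveness analyses estimate incremental cost per quality-adjusted life-year gained using EQ-5D-5L data". Uncertainty is to be shown by bootstrapping and cost-effectiveness acceptability curves.

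The schedule of the utility measure is fixed twice, and the two places agree. Table 1 ticks the EQ-5D-5L at T0 and T3 only, and Table 2 lists it as "EQ-5D-5L Economic Baseline, 12 months". The resource-use questionnaire has the same schedule: "Client Service Receipt Inventory Economic Baseline, 12 months".

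The Assessment schedule section says: "Outcome assessments are conducted at four time points by trained research assistants". These are baseline, 3, 6 and 12 months, and the 3-month visit falls at the end of the 12-session programme. Cognition, functional capacity, symptoms, disability, the MANSA and the WHOQOL-BREF global items are taken at all four.

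Costs have two sources (Measurement and valuation). For delivery, "Intervention costs are estimated using a micro-costing approach"; for the rest, "Service utilisation and indirect costs are assessed using the adapted CSRI".

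**The concern.** A QALY is the area under the utility curve over the year. With utilities at the two ends only, the shape between them has to be assumed, and a straight line is the usual assumption. That sits poorly with an intervention that ends at 3 months and with follow-up visits meant to show both the immediate effect and how long it lasts.

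The article gives no reason for leaving the EQ-5D-5L out at 3 and 6 months. It justifies a baseline-and-12-month schedule only for social cognition, on the ground of stability over shorter intervals. An analysis plan written later cannot recover utilities that were never collected.

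At stake are the incremental cost per QALY and the acceptability curves. Bootstrapping reflects sampling variation and would not reveal an error in the assumed path. The Dissemination strategy foresees policy briefs on cost implications, so the figures may be read outside the trial team.

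**Working it through.** **Inputs from the protocol article.** EQ-5D-5L at 0 and 12 months (Tables 1 and 2); visits at 0, 3, 6 and 12 months (Assessment schedule); 180 participants and 70–75% retention at 12 months (Sample size and pilot rationale). The article states no utility, QALY or cost figure, so there is no figure of its own to reproduce.

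**Assumptions.** Linear interpolation between measured points; no between-arm utility difference at baseline; a peak difference D of 0.03 to 0.10, for illustration only. Write d3, d6 and d12 for the between-arm utility differences at 3, 6 and 12 months.

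**Formulas** (time in years).

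- Two points: QALY difference = 1 × (0 + d12)/2 = 0.5·d12.
- Four points: 0.25·(0 + d3)/2 + 0.25·(d3 + d6)/2 + 0.5·(d6 + d12)/2 = 0.25·d3 + 0.375·d6 + 0.25·d12.

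The two agree only if 0.25·d3 + 0.375·d6 = 0.25·d12, that is, if the path averages out to the straight line.

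**Results by assumed path.**

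| Path (d3, d6, d12) | Four points | Two points | Two-point error | QALYs at D = 0.03 (four / two) | QALYs at D = 0.10 (four / two) |
|---|---|---|---|---|---|
| Reached at 3 months, sustained (D, D, D) | 0.875·D | 0.5·D | 43% too low | 0.026 / 0.015 | 0.0875 / 0.050 |
| Half kept (D, 0.75·D, 0.5·D) | 0.656·D | 0.25·D | 62% too low | 0.020 / 0.0075 | 0.066 / 0.025 |
| Gone by 12 months (D, 0.5·D, 0) | 0.4375·D | 0 | whole effect lost | 0.013 / 0 | 0.044 / 0 |
| Linear growth (0.25·D, 0.5·D, D) | 0.5·D | 0.5·D | none | 0.015 / 0.015 | 0.050 / 0.050 |
| Only after 6 months (0, 0, D) | 0.25·D | 0.5·D | twice too high | 0.0075 / 0.015 | 0.025 / 0.050 |

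For a given path the relative error does not depend on D. For the sustained path and a fixed incremental cost, the cost per QALY would be 0.875/0.5 = 1.75 times too high. For the path that is gone by 12 months, the QALY difference is zero and no finite ratio exists.

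**Attrition.** 180 × 0.25 = 45 and 180 × 0.30 = 54. Between 45 and 54 participants would have no utility after baseline, including any who attended at 3 or 6 months.

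**The case against.** The strongest reply is that this is a pilot. The economic work is labelled exploratory, Objective 7 promises a cost–consequence analysis, and no progression criterion in Table 3 uses a QALY, a cost or an acceptability curve. That stands and lowers the priority. It does not remove the point, because the label excuses imprecision better than it excuses a bias that existing visits could avoid.

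The size of the error also rests wholly on the assumed path. The article describes the intervention as working partly through habit formation, so gradual growth, for which the two-point estimate is right, is arguable. This stands too.

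A reader might infer more than the documents support, in four ways:

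- **That cost per QALY is bound to look too unfavourable.** This holds only for early effects; a late effect gives the opposite error.
- **That the analysis rests on 12-month completers.** No section says so. General analytic principles sets intention to treat, and Missing data plans multiple imputation where missingness in key outcomes exceeds 15%. It does not say whether the EQ-5D-5L is a key outcome. The MANSA and other measures at 3 and 6 months could inform imputation. What is missing is any interim EQ-5D-5L value.
- **That all costs depend on the 12-month questionnaire.** Intervention delivery is micro-costed and attendance is recorded during the programme; only service use and indirect costs come from the CSRI.
- **That part of the year goes uncosted.** The article gives no CSRI recall period, which may be in a supplement. A 12-month recall would cover the year, so the issue is at most long recall in a sample selected for cognitive impairment.

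**Conclusion.** The point holds for the QALY. Under linear interpolation and no baseline difference, the planned two-point schedule makes the QALY difference depend on the 12-month utility difference alone. On the paths examined, the error runs from losing the effect entirely, through 43% too low for an early sustained effect and none for linear growth, to twofold overstatement for a late effect. The documents offer nothing to choose between these paths, so the direction is unknown.

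At the assumed retention, 45 to 54 participants would have no post-baseline utility, which weakens any imputation. For costs, the concern is limited to possible long recall of service use and indirect costs. Priority is moderate to low: no trial decision turns on this, but the missing data cannot be recovered once the visits have passed.

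**What to change.** Add the EQ-5D-5L at T1 (3 months) and T2 (6 months) in Tables 1 and 2. State that QALYs are computed as the area under the curve over all four time points, with adjustment for baseline utility. The visits already take place face to face, so the cost is a protocol amendment and a few extra minutes of participant and interviewer time at each of two visits.

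Optionally, collect the CSRI at the same visits, with recall set to the time since the previous assessment. This would shorten recall of service use and indirect costs. It is a trade-off, because the questionnaire covers formal, informal, traditional and faith-based care as well as productivity losses, and it would lengthen an already full battery. Its value depends on the recall period now intended, which should be stated either way. Micro-costed intervention costs are unaffected.

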### Progression criteria for a definitive trial

As a pilot feasibility study, progression to a future definitive randomised controlled trial will be guided by prespecified criteria using a structured ‘traffic light’ framework. This framework integrates quantitative feasibility metrics with qualitative insights from the embedded process evaluation, allowing progression decisions to be informed not only by whether targets are met, but also by why they are met or missed.

**Green (Go):** Progression to a definitive trial will be recommended if recruitment rates meet or exceed 60%, retention at the 12-month follow-up meets or exceeds 70%, and intervention fidelity reaches at least 80% adherence to manualised content. Under this scenario, only minor protocol refinements would be required.**Amber (Amend):** If feasibility targets are narrowly missed but remain within a remediable range (eg, recruitment of 40%–59% or retention of 50%–69%), progression may still be recommended, conditional on targeted protocol modifications. Such modifications may include adjustments to recruitment pathways, increased participant reimbursement or refinements to intervention delivery identified through process evaluation findings.**Red (Stop):** Substantial shortfalls in feasibility (eg, recruitment below 40% or retention below 50%) will prompt a recommendation not to proceed to a definitive trial without fundamental redesign.

Progression to a future definitive trial will be guided by pre-specified 'traffic light’ criteria, integrating quantitative metrics with qualitative insights (table 3). Importantly, quantitative thresholds will not be interpreted in isolation. The Trial Steering Committee will explicitly prioritise triangulation with qualitative data to understand contextual drivers of feasibility outcomes. For example, if retention falls within the ‘Amber’ range but qualitative interviews indicate transport costs as the primary barrier, progression may still be endorsed contingent on addressing this barrier in future trial design.

**Table 3 T3:** Progression criteria for definitive randomised controlled trial (‘traffic light’ framework)

Domain	Green (Go)	Amber (Amend)	Red (Stop)
Recruitment rate	≥60% of eligible participants randomised	40%–59% randomised	<40% randomised
Retention at 12 months	≥70% retained	50%–69% retained	<50% retained
Intervention adherence	≥75% attend ≥9 sessions	60%–74% attend ≥9 sessions	<60% attend ≥9 sessions
Acceptability (CSQ-8)	Mean score ≥24	Mean score 20–23	Mean score <20
Intervention fidelity	≥80% adherence and competence	65%–79% adherence	<65% adherence
Qualitative feasibility	No major unresolvable barriers identified	Barriers identified but remediable	Fundamental barriers to delivery

Progression decisions will be based on triangulation of quantitative metrics with qualitative process evaluation findings rather than on any single criterion alone.

CSQ-8, Client Satisfaction Questionnaire-8.

### Patient and public involvement

Young people with lived experience of psychosis were actively involved throughout the development and design of the CognIFied study. Using YPAR principles, service users contributed to the cultural adaptation of the CCT curriculum, including refinement of language, examples, delivery style and perceived relevance of cognitive strategies to everyday life in the Nigerian context.

Youth collaborators also informed recruitment materials and strategies, ensuring that study information sheets and consent processes were accessible and culturally appropriate. Trained YRAs support recruitment and retention activities, under supervision, while maintaining clear boundaries to preserve voluntariness and informed consent.

Patients and caregivers will be involved in the interpretation and dissemination of study findings through a Youth Research Team, which will co-develop community-facing summaries, infographics and stakeholder engagement activities. Participants were not involved in setting the primary outcomes of the study, which were determined based on methodological guidance for pilot trials and clinical relevance.

## Ethics, participant safety, regulatory oversight and dissemination

### Ethical approvals

The study has received full ethical approval from the Health Research Ethics Committees of all participating institutions and is conducted in accordance with the Declaration of Helsinki, International Council for Harmonisation Good Clinical Practice guidelines, and the Nigerian National Code for Health Research Ethics.

Approvals were granted by:

Lagos State University Teaching Hospital (LASUTH): LREC/06/10/2373.Federal Neuro-Psychiatric Hospital, Yaba (FNPHY): FNPHY/HREC/2024/001/11/279.Neuropsychiatric Hospital Aro (NPHA), Abeokuta: PR/0031/25.

### Informed consent and capacity

Written informed consent will be obtained from all participants prior to enrolment. Given the presence of cognitive impairment in the study population, the consent process is deliberately iterative and supported. Research assistants will use structured teach-back methods to assess comprehension, asking participants to explain key aspects of the study in their own words before consent is accepted.

Participants aged 18–21 years provide autonomous consent in line with Nigerian legal standards. Where culturally appropriate and agreed by the participant, parallel parental or guardian awareness is encouraged, though not required. Individuals who lack decisional capacity at the time of screening due to acute symptom exacerbation are deferred until clinical stability is re-established.

#### Participant safety and adverse event monitoring

Participant safety is prioritised throughout the trial. A predefined safety protocol specifies procedures for managing participant distress, symptom exacerbation, suicidal ideation or behavioural risk. During assessments and intervention sessions, facilitators and research assistants complete a brief structured risk checklist. Participants expressing active suicidal ideation, intent or significant clinical deterioration are immediately referred to the treating psychiatrist, and same-day clinical review is arranged. All safety events are documented using a standardised adverse event form and reviewed weekly by the Trial Manager. A detailed safety protocol is provided in online supplemental file 5.

Although no significant safety risks are anticipated from either intervention, facilitators are trained to identify early warning signs of clinical deterioration and to activate appropriate referral pathways within routine care.

#### Post-trial care and access

All participants, regardless of trial arm allocation, will continue to receive routine psychiatric care at their treating hospitals following study completion. Participants who demonstrate significant clinical deterioration or adverse events during the study will be referred for appropriate clinical management within existing hospital services.

Following trial completion and pending favourable findings, the CCT intervention will be integrated into routine early psychosis services at participating sites, with all facilitators retained to support scale-up. Participants in both arms will be offered the opportunity to access CCT training materials and community-based support groups led by the Youth Research Team.

There are no anticipated harms requiring compensation beyond standard medical care. Nigeria does not have a statutory no-fault compensation scheme for research-related injury. In the unlikely event of research-related harm, participants will receive medical care through the hospital system at no additional cost.

### Data management and confidentiality

All study data are captured electronically using REDCap, hosted on secure, password-protected servers at Lagos State University College of Medicine. The database employs role-based access controls and maintains a complete audit trail. Personal identifiers are stored separately from research data in an encrypted linkage file accessible only to the Principal Investigator and Trial Manager.

Analytical datasets contain only anonymised participant identifiers. In line with funder requirements and local regulations, anonymised trial data will be securely archived for a minimum of 10 years following study completion.

